### Secondary objectives

•To compare the mean difference in systolic blood pressure (at least 6 mmHg) due to the intervention.

•To compare the mean change in total serum cholesterol (at least 4 mg/dl decrease) achieved in the adult hypertensive patients.

•To compare the mean change in glycaemic control in the adult type 2 diabetes patients (among registered hypertensive cases) receiving enhanced CVD-HTN care package (2%change in HbA1c) in comparison with the mean change for those receiving routine CVD-HTN care at the private health facilities(1%change in HbA1c).

•To compare the tobacco cessation rate in intervention arm (41%) and control arm (8%).

•Record adverse events of Cardiovascular disease (MI, angina) and cerebro-vascular disease (stroke) among the two arms of the study.

•To conduct incremental cost effectiveness analysis of managing adult hypertensive patients with or without associated conditions (Type 2 diabetes and hypercholesterolemia) at private care facilities in Punjab, Pakistan.

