### Hypothesis

•The enabling of private health facilities for cardiovascular disease intervention for adult hypertensive patients will improve the control of hypertension by decreasing mean systolic BP by at least 6 mm Hg.

•The enabling of private health facilities for cardiovascular disease intervention for adult hypertensive patients will improve the control of Blood glucose (HbA1C < 7.5%) and serum cholesterol (<200 mg/dl) by at least 15% (as compared to the current practice).

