### Statistical considerations

#### Sample size

A total of twelve clusters^c^ (i.e. six clusters in each trial arm) will be included in the study, with a minimum of 76 patients recruitment in each cluster and a total of 912 patients in the trial. The assumptions are: a) an intra-class correlation coefficient (ICC) of 0.02, b) design effect of 2.5 [4], c) and standard deviation of blood pressure as 11 mm [5] d) lost to follow-up of 25%. This sample size will give 94% power using 5% level of significance for detecting an assumed difference in the mean change of systolic blood pressure of 6 mm Hg between the intervention and the control arm [6,7].

For a sub group analysis of hypertensive patients with concomitant type-II diabetes, the main assumption is that 27.6% of the recruited hypertensive will have type-II diabetes i.e. 21 patients out of 76 hypertensive recruited at each clinic will be have diabetes [3]. The proposed sample size will give 86% power using 5% level of significance for detecting an assumed difference in mean change of HbA1c of 1% [8,9] between the intervention and the control arms. The assumed standard deviation of HbA1c is 2% [10], and intra-cluster correlation is 0.02 [6,7].

For a sub group analysis of hypertensive patients with concomitant hyper-cholesteremia, the main assumption is that 39.3% of the recruited hypertensive will have hyper-cholesteremia i.e. 30 patients out of 76 hypertensive recruited at each clinic will be have hyper-cholesteremia [3]. The proposed sample size will give 100% power using 5% level of significance for detecting an assumed difference of 4.9 mg/dl [11] between the group means. The assumed standard deviation is 2.9 mg/dl [11], and intra-cluster correlation is 0.02 [6,7].

For a sub group analysis those hypertensive patients who smoke, the main assumption is that 34.5% of the recruited hypertensive will be tobacco smokers i.e. 27 out of 76 hypertensive recruited at each clinic will be smokers [3]. The proposed sample size will give 100% power using 5% significance level for detecting a difference between the group proportions of 0.33 when the intra-cluster correlation is 0.02 [6,7].

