#### Planned statistical tests

Cluster and individual level analysis will be done on SPPS version 17. Histograms will be made for the continuous variables e.g. age, systolic blood pressure, diastolic blood pressure, fasting blood glucose, HbA1c etc.

Descriptive statistics will be computed: proportion for categorical variables, mean and standard deviation for continuous variables having normal distribution, median and inter quartile range for continuous variables having skewed distribution.

a. Difference of mean systolic blood pressure at baseline and then at 15 months of follow up between the intervention and the control arm will be measured by independent t-test. Difference of mean systolic blood pressure at baseline and at 15 months of follow up in the intervention arm/control arm will be measured by the paired sample t-test. Mean change of systolic blood pressure between intervention and the control arm will be measured by t-test. P-value of < 0.05 will be considered significant.

b. Difference of mean HBA1c at baseline and then at 15 months of follow up between the intervention and the control arm will be measured by independent t-test. Difference of mean HBA1c at baseline and at 15 months of follow up in the intervention arm/control arm will be measured by the paired sample t-test. Mean change of HBA1c between intervention and the control arm will be measured by t-test. P-value of < 0.05 will be considered significant.

c. Difference of mean total cholesterol levels at baseline and then at 15 months of follow up between the intervention and the control arm will be measured by independent t-test. Difference of mean total cholesterol levels at baseline and at 15 months of follow up in the intervention arm/control arm will be measured by the paired sample t-test. Mean change of total cholesterol levels between intervention and the control arm will be measured by t-test. P-value of < 0.05 will be considered significant.

d. Proportions of adult Type 2 diabetes patients having htn control (<140/90) in the two arms will be compared by conducting chi-square test. P-value of < 0.05 will be considered significant.

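### The second hypothesis, on HbA1c and cholesterol control with a 15% target, has no matching test, and the only planned test of proportions matches no stated objective or hypothesis

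*Protocol article*

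**What the plan says.** The Hypothesis section has two entries. The first is on mean systolic pressure. The second says that enabling the facilities "will improve the control of Blood glucose (HbA1C < 7.5%) and serum cholesterol (<200 mg/dl) by at least 15% (as compared to the current practice". It is worded for adult hypertensive patients. It does not say whether 15% is absolute or relative, and no control-arm rate is given.

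The Secondary objectives treat the same two markers as means: "To compare the mean change in glycaemic control in the adult type 2 diabetes patients (among registered hypertensive cases", with 2% against 1% change in HbA1c, and "To compare the mean change in total serum cholesterol (at least 4 mg/dl decrease) achieved in the adult hypertensive patients".

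Planned statistical tests follows the objectives. Item b: "Mean change of HBA1c between intervention and the control arm will be measured by t-test". Item c: "Mean change of total cholesterol levels between intervention and the control arm will be measured by t-test". Item d is the only comparison of proportions: "Proportions of adult Type 2 diabetes patients having htn control (<140/90) in the two arms will be compared by conducting chi-square test". Item a covers systolic pressure, item e regression for drug-class confounding, and item f cost-effectiveness.

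Sample size gives 86% power "for detecting an assumed difference in mean change of HbA1c of 1"% in diabetics, and 100% power for a 4.9 mg/dl difference between group means in hypercholesterolaemic patients. The only power for a proportion is for smoking, a difference of 0.33.

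**The concern.** A hypothesis defined by thresholds and a 15% improvement is a statement about the proportion of patients controlled. A t-test on mean change does not answer it: a mean can fall without moving many patients across a threshold, and the reverse can also happen. The one test that does compare a control rate uses blood pressure in diabetics, an endpoint and group that are paired nowhere else in the article.

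As it stands, one of two stated hypotheses could be neither supported nor refuted by the listed analyses. Anyone wishing to report on it would have to choose the population, the method and the meaning of 15% later, possibly with the data in view. The listed control-rate result would have no declared purpose, and its chi-square test would treat patients of one facility as independent.

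**Working it through.** **1. Hypothesis against tests.**

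| Quantity | Hypothesis | Objective | Planned test | Stated power |
|---|---|---|---|---|
| HbA1c below 7.5%, 15% better | second | none | none | none |
| Cholesterol below 200 mg/dl, 15% better | second | none | none | none |
| Mean change in HbA1c | none | secondary | item b | 86% |
| Mean change in cholesterol | none | secondary | item c | 100% |
| BP below 140/90 in diabetics | none | none | item d | none |

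Objectives, powers and items b and c agree with one another. The second hypothesis and item d are the two loose ends.

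**2. The stated powers.** Inputs from Sample size: 6 clusters per arm, ICC 0.02, 5% level (taken as two-sided). For HbA1c, m = 21 diabetics per cluster, SD 2, difference 1.

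- Design effect = 1 + (21 − 1) × 0.02 = 1.40.
- Effective n per arm = 6 × 21 / 1.40 = 90.
- SE = 2 × √(2/90) = 0.298; noncentrality = 1/0.298 = 3.35.
- Noncentral t with 12 − 2 = 10 df (critical value 2.228): power 85.5%, matching 86%.

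A normal approximation after 25% loss (m = 15.75) also gives 85.5%. Either way 86% is a power for means. For cholesterol, m = 30 gives design effect 1.58 and effective n 113.9. SE = 2.9 × √(2/113.9) = 0.384, noncentrality = 4.9/0.384 = 12.8, and power 100%. Both figures are correctly labelled.

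**3. Power for a 15-point gain in a control rate.** With p1 = p0 + 0.15 and n the effective number per arm, SE = √{[p0(1 − p0) + p1(1 − p1)]/n}, and power comes from the noncentral t with 10 df at 0.15/SE. The control-arm rate p0 is an assumption, 0.10 to 0.70.

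Example, HbA1c in diabetics, p0 = 0.40: SE = √[(0.24 + 0.2475)/90] = 0.0736; noncentrality = 0.15/0.0736 = 2.04; power 45%.

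| Population | m per cluster | Design effect | Effective n per arm | Power |
|---|---|---|---|---|
| Diabetics | 21 | 1.40 | 90.0 | 45–68% |
| Diabetics, 25% loss | 15.75 | 1.295 | 73.0 | 38–59% |
| Hypercholesterolaemic | 30 | 1.58 | 113.9 | 54–78% |
| Hypercholesterolaemic, 25% loss | 22.5 | 1.43 | 94.4 | 47–70% |
| All hypertensives | 76 | 2.50 | 182.4 | 74–93% |
| All hypertensives, 25% loss | 57 | 2.12 | 161.3 | 69–90% |

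The low end is near p0 = 0.425 and the high end is at p0 = 0.10.

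**4. If 15% is relative** (p1 = 1.15 × p0), the same method before loss gives about 6–32% (diabetics), 6–39% (hypercholesterolaemic) and 6–56% (all hypertensives).

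**5. The chi-square test in item d.** At the protocol's own ICC, an unadjusted test has a true two-sided error rate of about 2 × [1 − Φ(1.96/√DE)], where DE is the design effect. With DE = 1.40 this is 9.8%; with DE = 1.295 (after loss) it is 8.5%, against a nominal 5%.

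**The case against.** Four points on the other side deserve weight.

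- Items b and c compare both markers between arms, so the substance of the second hypothesis is examined. This stands: what lacks a test is only the threshold and 15% form.
- A reader might infer that the article claims 86–100% power for the second hypothesis. It does not. Sample size says in terms that these figures are for differences in means, so there is nothing to correct there.
- A reader might also infer that the trial has even odds or less of detecting the 15% gain. The documents do not support that. The result depends on a control-arm rate that is not given, on whether 15% is absolute, and on the population. The hypothesis is worded for adult hypertensive patients, and analysing all of them gives 74–93% before loss.
- Nor does item d amount to neglect of hypertension control in non-diabetic patients. The first hypothesis defines that control as a fall in mean systolic pressure, and item a tests it without restriction to diabetics. The diabetic subgroup itself is named in the secondary objectives and sized. Only its pairing with BP below 140/90 is unexplained.

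The pilot phase allows assumptions and methods to be revised. That is an occasion to repair the mismatch and does not itself repair it. Item d may be a slip for glycaemic control in diabetics, but the text does not say so, and cholesterol control would still have no test.

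**Conclusion.** The concern holds as a mismatch inside the article. The second hypothesis is about control rates, the listed tests of those markers are about means, and the single test of proportions serves no stated objective or hypothesis and ignores clustering. The primary outcome is unaffected, and the correction should be made.

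No power is stated for the second hypothesis, and none can be fixed from the document alone. On the assumptions shown (15 percentage points, ICC 0.02, 10 df, control-arm rates of 10–70%), power after loss runs from 38% to 90% depending mainly on whether the subgroups or all hypertensives are analysed. A relative 15% would give far less. The width of that range is itself a reason to define the hypothesis before it is tested.

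**What to change.** Choose one of two routes.

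1. **Keep the hypothesis.** Add comparisons at 15 months of HbA1c below 7.5% in diabetics and of total cholesterol below 200 mg/dl in a named population. Use a t-test on the 12 facility proportions, or a mixed or GEE binary model with small-sample correction. Report both as secondary estimates with confidence intervals. State whether 15% is absolute or relative, and give the power as a range with its assumptions, not as a single figure.
2. **Restate the hypothesis** as the mean differences already used in the secondary objectives, the sample-size section and items b and c. This is the simpler repair.

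On either route, correct item d if it is a slip, or tie it to a stated objective, and replace the plain chi-square test with the same cluster-respecting method.

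The cost is wording only, since HbA1c, cholesterol and blood pressure are already to be measured. The first route may mean stating a less favourable power for the second hypothesis.

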### Interventions

#### Intervention arm

Quality care will be delivered to adult hypertension patients, through enabled private healthcare facilities. The inputs for delivering quality care at enabled facilities will include: a) context sensitive operational guidelines^b^, b) supplement equipment and communication, c) training and supervisory support, d) patient education materials. The care delivery dimensions to be addressed will include: a) enhanced screening and diagnosis, b) standardized prescription, c) interactive education of patient and family, d) follow-up and adherence, e) recording, reporting and monitoring, f) referral linkage with respective district hospital, g) district health office engagement and support, and h) technical support for in-country research uptake.

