#### Control arm

The control for comparison is the current care practices (for hypertension and associated conditions) at the private health care facilities. The only addition will be a) enhanced screening and diagnosis, b) introduction of HTN-CVD register for collecting core data set on patients attending these control facilities. In ‘current practice’, each practitioner manages HTN-CVD cases, as per his/her self-determined regimen and without reference to any specific guidelines and/or tools.

The health staff at a facility will offer the same care package to all its HTN-CVD cases, regardless of their social strata and other preferences. This will reduce the chances of intra-cluster contamination as well as strengthen and simplify the implementation of prospective evaluation. All trial patients will be asked to arrange their prescribed drugs, so that the trial reflects the real life practice in private health care delivery system.

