#### Inclusion/exclusion criteria

Among these private facilities ,all newly diagnosed hypertensive (systolic blood pressure >140 mm Hg, diastolic blood pressure >90 mm Hg) male and female patients aged 25 years or more from the catchment population of the respective facility will be included, after an informed consent. The patients to be excluded from the trial are: a) pregnant women, b) persons with advanced chronic disease, c) person with conditions that cause secondary hypertension, d) person with known history of hypertension and/or CVD treatment in the past, e) person not likely to stay in the area for the required follow-up period of 15 months.

Patients who are pregnant and have hypertension will be referred to a gynecologist, patients with advanced chronic disease to a general medical practitioner, and those with a known history of hypertension and/or CVD treatment in the past will be referred to a cardiologist. Only patients who are new cases of hypertension are included in the trial. People with known hypertension are excluded from the trial as they would already be on some sort of antihypertensive drug regimen which may mask the effects of our intervention.

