#### Recruiting participants

The eligible for inclusion patients will be informed and offered to participate (see inclusion/ exclusion criteria above). The patient is recruited only if he/she consents to participate.

Once recruited, each patient in the:

– control arm will be offered standardized diagnosis and care as per current practice, whereas intervention arm will be offered an enhanced HTN-CVD care including standardized diagnosis, prescription, follow-up, and monitoring.

– intervention arm will also be educated on life style modifications recommended for the individual, whereas control arm patients will receive information brochure.

– both arms will be asked to arrange the prescribed medicine through their own sources. However, access to baseline BP, HbA1c, cholesterol examination will be facilitated, for both arms, through trial resources.

Both arms will be requested to adhere to the treatment protocols.

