e. Residual confounding will be taken care of by multivariable regression (MLR)analysis. Strartified MLR will be done with the different groups of medications being as different strata eg, Beta blockers, ACE inhibitors, ARBs, Calcium channel blockers etc. being as different strata. Results will be presented in a stratified analysis. This will take care of confounding my different effects on BP from different groups of anti hypertensive drugs.

f. Incremental cost and effect will be calculated for the intervention and the control arms and subsequently cost: effect ratio will be calculated.

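### The only adjusted analysis described is stratified by antihypertensive drug class, which is set after randomisation and which the intervention can change, so its results do not estimate the total effect

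*Protocol article*

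**What the plan says.** Item e under Planned statistical tests proposes multivariable regression to deal with residual confounding. It then specifies "Strartified MLR will be done with the different groups of medications being as different strata", naming beta blockers, ACE inhibitors, ARBs and calcium channel blockers as examples, and says the results will be shown by stratum. The reason given is: "This will take care of confounding my different effects on BP from different groups of anti hypertensive drugs".

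Other sections bear on what drug class is in this trial:

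- **Intervention arm** lists the care dimensions of the package: "a) enhanced screening and diagnosis, b) standardized prescription, c) interactive education of patient and family", among others. Recruiting participants repeats this: "intervention arm will be offered an enhanced HTN-CVD care including standardized diagnosis, prescription, follow-up, and monitoring".
- **Control arm** says that "each practitioner manages HTN-CVD cases, as per his/her self-determined regimen and without reference to any specific guidelines and/or tools".
- **Inclusion/exclusion criteria** says "Only patients who are new cases of hypertension are included in the trial", and excludes any "person with known history of hypertension and/or CVD treatment in the past".
- **Phases of the trial** places randomisation of facilities among the arrangements made before patients are registered.
- **Planned statistical tests, item a** compares mean change in systolic pressure between arms by t-test, with no reference to drug class.

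**The concern.** A confounder has to precede, or at least not result from, the exposure. Drug class here is chosen after the facility has been randomised, by a doctor whose prescribing the intervention is meant to change. Comparing arms within class does two things that no baseline adjustment does. It holds fixed a route by which the package may lower blood pressure. It also compares intervention patients given a class under a guideline with control patients given it under individual judgement, and these need not be similar patients.

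This matters because item e is the only adjusted analysis the article describes. The section on bias, error and limitations concedes that simple randomisation of the facilities does not balance baseline covariates. With twelve facilities, chance imbalance is a real possibility, and readers would then turn to item e. They would find estimates with a bias of their own.

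**Working it through.** **Is drug class a confounder? The text, step by step.**

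1. *Timing.* Facilities are randomised before registration, and only new cases without past treatment are eligible. An eligible patient has no antihypertensive class at baseline, so every class is assigned after randomisation.
2. *Reach of the intervention.* Standardised prescription is a named part of the package, while control doctors follow their own regimens. The rule for choosing a drug differs between arms by design.
3. *Link to outcome.* Item e itself says the classes differ in their effect on blood pressure.

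By the article's own account, class follows allocation, can be changed by it and affects the outcome. That makes it a possible mediator.

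**How far could this matter?** The article states no figure to reproduce. Both illustrations below use assumed inputs. Effects are mmHg of systolic reduction, class is binary, and clustering is ignored.

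*Illustration 1: blocked pathway only.* Take the planned difference of 6 mmHg and SD 11 from Sample size. Assume about 80% of intervention patients and 40% of controls receive one class, with no severity effect on outcome. If a share *f* of the effect runs through class, the within-class estimate is 6 × (1 − *f*):

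| Share through class | Unstratified | Class-adjusted |
|---|---|---|
| 0% | 6.0 | 6.0 |
| 25% | 6.0 | 4.5 |
| 50% | 6.0 | 3.0 |
| 75% | 6.0 | 1.5 |

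Now let unmeasured severity drive class choice in the control arm and shift the outcome by 3 mmHg per SD. With a 50% share the true direct effect is 3.0, but the two strata give 4.1 and 1.5. With a 0% share, where class has no effect on pressure, the strata give 7.0 and 4.6 instead of 6.0.

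*Illustration 2: net direction.* Assume logit P(class) = −0.85 + 1.7 × arm + 0.8 × severity, which gives about 68% against 32% use. Let reduction = 2 × arm + *c* × class − 5 × severity + noise (SD 10), where *c* is the extra reduction from that class. The total effect is 2 + *c* × (0.68 − 0.32), using unrounded proportions. Within class, severity differs between arms by about 0.25 SD, which adds about 5 × 0.25 ≈ 1.3 to the direct effect of 2.0:

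| *c* (mmHg) | Total effect | Crude within-class estimates |
|---|---|---|
| 8 | 4.9 | 3.3 and 3.2 |
| 4 | 3.4 | 3.3 and 3.3 |
| 2 | 2.7 | 3.3 and 3.3 |
| 0 | 2.0 | 3.3 and 3.3 |

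At *c* = 8 the strata understate the total effect; at 2 or 0 they overstate it. If the severity effect on response is reversed, the strata at *c* = 8 fall to about 0.7. If severity is measured and entered as a covariate, they return about 2.0. That is the direct effect, and still not the total.

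**The case against.** **The main comparison is elsewhere.** A reader might infer that the trial's primary result is compromised. The article does not support that. The primary objective is mean change in systolic pressure, item a compares it between arms without conditioning on class, and the analysis is by intention to treat. The sentence about presenting stratified results belongs to item e and does not say they replace item a. This objection stands and sets the severity.

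**The package must look weaker.** A reader might also infer that stratifying necessarily hides part of the benefit, or a fixed share such as a third (3.3 against 4.9). That share comes from one set of assumed inputs. At smaller class differences it vanishes or reverses.

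**Item e is a regression, not a crude comparison.** Measured severity in the model would reduce the selection component. That is true, but the article lists no covariates, and adjustment does not reopen the blocked pathway.

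**Class may not shift at all.** Standardised prescription could act on dose, titration or adherence, and the operational guideline cited in the endnotes is not reproduced. A different class mix by arm is plausible but not documented. If the mix did not differ, the pathway through class would be small. Selection within strata could remain, because the rules for choosing a class would still differ.

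**The methods are open to revision.** The pilot phase allows the statistical methods to be modified. That offers an occasion for the change but does not make it.

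**Conclusion.** The point holds for item e alone. Drug class is set after randomisation and can be changed by the intervention, so calling it a confounder is wrong. The class-stratified results do not estimate the total effect of the package and are not protected by randomisation. This rests on the article's text and on no numerical assumption.

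The size and net sign of the distortion are unknown, because the article gives no class mix by arm and no effect by class. The illustrations show only that both directions are possible. The point should be fixed, as a fault in a supporting analysis.

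**What to change.** In item e, delete the drug-class strata and the sentence giving confounding by drug effects as the reason. Then:

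- Fit the multivariable model without stratification, using only covariates measured before treatment that the trial collects, for example baseline systolic pressure, age, sex, diabetes and smoking.
- Handle clustering with a random facility effect or a cluster-level analysis. Fixed facility effects will not do: each facility lies wholly in one arm, so they are collinear with arm and the treatment effect could not be estimated.
- Report drug class by arm descriptively, as a process measure of what the package changed.
- Label any class-specific or mediation analysis as exploratory, and state that it does not estimate the total effect.

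The cost is a change of analysis wording, best made before outcome data are seen. The article does not list the fields of the CVD card or the trial registration form, so the covariates should be checked against those forms. Facility patient load, for instance, appears only as a factor that stratified randomisation could have used. No clinical procedure changes.
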